## Data collection protocol

The EEG data collection protocol will involve monitoring patients with severe traumatic brain injury (TBI) during the subacute phase of the trauma. The subacute phase is defined as beginning on the seventh day following the traumatic event [[23], [24], [25]]. EEG recordings will be performed immediately after the patient's transfer from the intensive care unit (ICU) to the hospital ward. This timing was chosen to account for the complex and dynamic nature of the ICU environment, while the hospital ward is expected to offer a more stable and controlled setting for optimal EEG acquisition. The subacute phase was selected because, in comparison to the acute phase, patients are generally more stable during this period, which is also when key physiological recovery processes and neuronal reorganization typically occur [[26], [27], [28]].

To comprehensively assess the functional and cognitive status of patients throughout the study, functional scales will serve as a critical component for comparing and validating the predictive potential of EEG in relation to TBI events. These functional scales, as detailed in Table 2, will be administered at key time points: ICU discharge, hospital discharge, and at three, six, and twelve months post-TBI.

**Table 2 tbl0002:** Description of functional scales.

Scale	Description
Glasgow Coma Scale (GCS)	Assesses the patient's level of consciousness based on three parameters: eye opening, verbal response, and motor response. The score ranges from 3 to 15, with lower scores indicating more severe coma.
Dementia Rating Scale (DRS)	Used to assess cognitive function in dementia patients. The score is determined by the patient's performance on memory, orientation, and ability to perform daily activities. The score ranges from 0 to 144, with lower scores indicating greater severity.
Functional Independence Measure (MIF)	Assesses the functional independence level of patients in daily activities such as eating, dressing, and mobility. Scores range from 18 to 126, where 18 indicates total dependence and 126 indicates total independence.
Functional Ambulation Categories (FAC)	Measures the patient's ability to walk based on the support needed. Categories range from 0 (no walking) to 5 (independent walking).
Rancho Los Amigos Scale (RLA)	Assesses the level of neuropsychological recovery after a brain injury. There are seven levels ranging from total absence of response (Level I) to full recovery and return to social and professional activities (Level VII).

### EEG protocol

The EEG protocol will be performed with the patient in a resting, relaxed, and awake state, with eyes closed. EEG recordings will be conducted using the Startism 20 system (Starstim® tES-EEG systems), a 20-channel device with specialized electrodes designed for EEG monitoring (Fig. 1). The settings will include a time constant of 0.3 seconds and a high-frequency cutoff at 30 Hz. To minimize potential artifacts that could compromise the quality of the recordings, the EEG will be performed in a quiet environment with low lighting to ensure optimal conditions.

**Fig. 1 fig0001:**
[figure not shown]
EEG equipment.

All cerebral electrical activity will be analyzed using computerized spectral EEG analysis and topographic brain mapping. Electrodes will be positioned according to the international 10–20 system, as shown in Fig. 2. The electrode impedance will be kept below 3 kΩ, with the earlobes serving as the reference. Prior to electrode placement, patients will be instructed to wash their hair with neutral shampoo and ensure it is dry, which will help minimize scalp impedance. During the electrode setup, conductive gel will be applied to the electrode sites to enhance signal quality and ensure proper contact with the scalp.

**Fig. 2 fig0002:**
[figure not shown]
EEG montage according to the 10–20 system.

### EEG data recording and treatment

EEG data will be continuously recorded in a digital spectral file using the NIC2 software (Starstim® tES-EEG systems) and stored for subsequent analysis. The vigilance state of participants will be continuously monitored throughout the EEG recording process. The entire procedure will last 20 minutes, and all steps will be performed by a researcher trained in EEG techniques.

Biomarkers related to brain activity patterns will be considered for analysis in this study. Abnormal brain activity patterns will be evaluated for each participant and categorized, focusing on significant changes in the frequency and amplitude of brain waves across all monitored regions. Table 3 provides a detailed description of EEG wave patterns and their characteristics in relation to the monitored brain areas, functions, and potential alterations associated with traumatic brain injury (TBI).

**Table 3 tbl0003:** waveforms and functions in TBI.

Wave Type	Frequency (Hz)	Brain Region	Function	Alterations	Condition/Events	Interpretation	Waveform Example	References
Delta	0.5 - 4	Deep brain	Deep sleep, regeneration	Significant increase	Moderate to severe TBI	Indicates reduced cortical activity, coma state; impairment of brain function		Zetterberg, H., et al. (2013). *Nature Reviews Neurology*
Theta	4 -8	Hippocampus, temporal cortex	Creativity, meditation, light sleep	Increase	Mild to moderate TBI, concussion	Reflects altered consciousness and difficulties in attention/memory		Guskiewicz, K. M., et al. (2017). *Sports Medicine*
Alpha	08 – 12	Occipital cortex	Relaxation, alert state	Decrease	TBI and PTSD	Reduction is associated with difficulties in relaxation and hyperexcitability		Moffat, S. D., & Hampson, E. (2018). *Psychological Science*
Beta	12 - 30	Frontal, parietal cortex	Concentration, mental activity	Increase or irregularity	TBI with psychiatric sequelae	High levels indicate anxiety and cognitive overload; responses to post-traumatic stress		Kuperman, V., et al. (2015). *Neuropsychology*
Gamma	30 - 100	Various regions	Information processing	Irregular patterns	TBI with cognitive complications	Irregular patterns associated with processing disorders		Siegel, M., et al. (2012). *Nature Reviews Neuroscience*

### Collection and clinical information

Sociodemographic data for all participants will be collected from medical records, including information on age, gender, education level, occupation, and other relevant factors. Additionally, clinical data obtained during hospitalization will be recorded, such as vital signs, pupillary response characteristics, need for intubation, surgical interventions performed, imaging results, length of stay in the intensive care unit (ICU), and total hospitalization duration, among other clinical parameters. These data are crucial for a comprehensive characterization of the patients' social and clinical profiles. This detailed information will enable a more thorough analysis of the variables associated with traumatic brain injury (TBI) and will contribute to the development of more precise and individualized management strategies.

### Statistical analysis

The collected EEG data will be pre-processed using MATLAB software, equipped with the EEGLAB plugin (Neuroelectrics), for initial processing, including noise filtering, artifact removal, and extraction of specific features such as frequency and amplitude of brainwave bands [29]. Statistical analysis will involve the development of a predictive model based on categorized characteristics, such as frequency bands and amplitudes of EEG signals, to correlate these parameters with clinical outcomes [30].

Binomial logistic regression analyses will be performed using Stata (version 17) to explore the predictive power of EEG biomarkers. SPSS (version 28) will also be employed to conduct initial descriptive analyses, including variable distribution, normality tests (e.g., Shapiro-Wilk), and group comparisons using appropriate statistical tests (e.g., *t*-test, Mann-Whitney, or ANOVA, depending on data distribution). These analyses will ensure data adequacy and identify preliminary relationships between EEG parameters and clinical outcomes [31,32].

Additionally, ROC curves will be generated using SPSS, and the area under the curve (AUC) will be calculated to evaluate the sensitivity and specificity of predictive models. Model robustness will be validated through cross-validation, and additional tests, such as the Hosmer-Lemeshow test, will be applied to assess the logistic model's fit to the data [33].

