## Description of protocol

This study aims to contribute to the understanding of the incidence of TBI and its associated biomarkers in a trauma care setting, with a particular focus on electroencephalography (EEG) as a potential diagnostic tool for early detection and monitoring of TBI. By integrating EEG data, the study seeks to provide valuable insights into the relationship between brain electrical activity and TBI, ultimately advancing clinical outcomes in the management of TBI patients.

This prospective cohort study will be conducted at a trauma reference hospital in Vitória, Espírito Santo, Brazil. The study population will include all patients admitted with traumatic injuries, who will be monitored by researchers through daily entries in their medical records. This will enable the identification of cases of traumatic brain injury (TBI) and determine the eligibility of patients for inclusion in the study. The inclusion and exclusion criteria are detailed in Table 1. Informed consent and comprehensive details about the study protocol will be provided to participants at the time of the first data collection, ensuring full understanding of the research procedures and objectives.

**Table 1 tbl0001:** Inclusion and exclusion criteria for the study.

Inclusion criteria	Exclusion criteria
Adults of both sexes, aged 18 or older	Under 18 years old
Glasgow Coma Scale (GCS) ≤ 8 at any time during hospital stay	Open TBI
Admitted to an Intensive Care Unit (ICU)	History of previous neurological diseases
Informed consent signed	History of previous psychiatric diseases

Sample size estimation was based on a two-tailed hypothesis test with a medium Pearson correlation coefficient (r = 0.3), a significance level (α) of 0.05, and a statistical power (1 - β) of 0.80. Using these parameters, a target sample size of 84 individuals was determined to provide adequate power for detecting clinically meaningful relationships between variables. The sample size calculation was performed using GPower software [22], a widely used tool for power analysis in experimental design.

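### The 84 patients are sized for a correlation of two uncategorised variables, but the planned model is a binomial logistic regression on categorised EEG features, so the stated 80% power does not apply to the functional scales

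*Protocol article*

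**What the plan says.** **Sizing.** Under Description of protocol, "Sample size estimation was based on a two-tailed hypothesis test" with a Pearson correlation of 0.3, "a significance level (α) of 0.05" and "a statistical power (1 - β) of 0.80". The result is 84 individuals.

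**Predictors.** The Statistical analysis section plans the "development of a predictive model based on categorized characteristics, such as frequency bands and amplitudes of EEG signals". The section on EEG data recording and treatment adds: "Abnormal brain activity patterns will be evaluated for each participant and categorized".

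**Model.** "Binomial logistic regression analyses will be performed using Stata (version 17) to explore the predictive power of EEG biomarkers". ROC curves, AUC and the Hosmer-Lemeshow test go with it. No linear or ordinal regression is named. The t-test, Mann-Whitney and ANOVA comparisons are described as initial and preliminary.

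**Outcomes.** The Data collection protocol makes the functional scales the yardstick for the predictive value of EEG. Table 2 gives their ranges. For the Functional Independence Measure (MIF): "Scores range from 18 to 126, where 18 indicates total dependence and 126 indicates total independence". The DRS runs from 0 to 144, the FAC from 0 to 5 and the GCS from 3 to 15, and the RLA has seven levels. The Abstract also names mortality, which is binary by nature.

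**The concern.** A sample size holds for the analysis it was computed for. The correlation calculation uses all the information in both variables. A binomial model needs a two-level outcome, so each functional scale has to be cut once. If the EEG measures are cut as well, information is lost on both sides.

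Cutting treats patients just either side of the threshold as different and all patients on one side as alike, which weakens the association that can be seen. At stake is whether a true relation of the planned size would be detected with 84 patients. A null result for functional recovery would be less informative than the stated power suggests.

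**Working it through.** **Inputs from the Protocol article:** r = 0.3, two-sided alpha 0.05, power 0.80, N = 84 (Description of protocol); scale ranges (Table 2); binomial logistic model on categorised EEG characteristics (Statistical analysis).

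**Assumptions, not in the article:** EEG feature and outcome are bivariate normal before any cut; one predictor; no dropout; outcome split 50/50 or 70/30; EEG split, where there is one, at the median.

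**Step 1. Reproduce the stated figure.** By Fisher's z, N = ((1.960 + 0.842)/atanh(0.3))² + 3, with atanh(0.3) = 0.3095, gives 84.93, within one patient of 84. With the usual bias correction, power at 84 is Φ((0.3095 + 0.3/(2 × 83)) × √81 − 1.960) = Φ(0.842) = 0.800. Simulation (50,000 runs) gives 0.799. The figure of 84 is right for two uncategorised variables.

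**Step 2. Cut the outcome only.** A median split of one variable lowers the correlation to 0.3 × √(2/π) = 0.239. The efficiency is 2/π = 0.637, as if about 36% of the sample were discarded. Power at 84 by the same formula is 0.599; simulation gives 0.600. With a 70/30 split, simulation gives 0.555.

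**Step 3. Cut both at the median.** φ = (2/π) × asin(0.3) = 0.194, and 0.194²/0.3² = 0.42, so about 42% of the information is kept. This equals comparing proportions of 0.597 and 0.403 with 42 patients each: power 0.426, simulation 0.430. With the outcome at 70/30, simulation gives 0.393.

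**Step 4. Check with the logistic Wald test** (3,000 simulated trials per case), the type of model the article names.

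| Handling at N = 84, r = 0.3 | Outcome split 50/50: power (logistic Wald) | Outcome split 70/30: power (logistic Wald) |
|---|---|---|
| EEG continuous, outcome binary | 0.60 (0.58) | 0.56 (0.55) |
| EEG in 3 to 5 ordered levels, outcome binary | 0.51 to 0.55 | 0.47 to 0.51 |
| EEG split at median, outcome binary | 0.43 (0.41) | 0.39 (0.39) |

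Nothing cut: 0.80. A more uneven 80/20 outcome split lowers power further, to 0.49 with EEG continuous and 0.34 with EEG split at the median.

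**Step 5. Size needed for 80% power.** One median split: ((1.960 + 0.842)/atanh(0.239))² + 3, about 135 patients. Both split at the median: about 208.

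**The case against.** Several points on the other side have force.

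- **The logistic outcome is not named.** That functional scores will be the dependent variable is inferred from the role the article gives the scales. For mortality, a binomial model discards nothing on the outcome side. This stands, and the point is limited to the functional scales.
- **The word *categorized* may mean only sorting features by frequency band, with amplitude kept numeric.** This reading is possible, although the article lists amplitudes as well as bands and also speaks of categorising each participant's patterns. On this reading only the outcome is cut, and the 56-60% figures apply.
- **A reader might infer that power is roughly halved.** That needs a two-level EEG variable as well as a binary outcome. The article fixes no number of levels and no cut, so halving is the lower end of a range and not a property of the plan.
- **A reader might also infer that cutpoints will be chosen from the data and will inflate the apparent prediction.** Nothing in the text says so, and cross-validation is planned. The missing cutpoints are detail that an article may leave to the full protocol.
- **ROC curves, sensitivity and specificity need a binary outcome, and power for an association is not a measure of predictive performance.** Both are true. They justify a binary analysis for the ROC curve. They do not make a correlation-based 80% the power of that analysis.
- **A binary poor outcome can absorb deaths before follow-up.** A proportional-odds model can do so too, with death as the worst level; a linear model would need a further rule. This bears on how the remedy is carried out and does not remove the mismatch.

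The preliminary group comparisons do not close the gap: they are labelled preliminary and are not the predictive model.

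**Conclusion.** The point holds for the functional scales. The calculation behind 84 is correct for a Pearson correlation, but the named model is of a different kind, and the stated 80% does not carry over to it. With outcome splits between 50/50 and 70/30, power is about 56-60% if only the outcome is cut, a loss of 20 to 24 percentage points. It is about 39-43% if the EEG feature is dichotomised too, a loss of 37 to 41 points. Three to five ordered EEG levels fall in between.

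These figures rest on bivariate normality, a true correlation of 0.3, a single predictor and no dropout. They do not apply to mortality, for which logistic regression is suitable. The study remains interpretable. The loss is avoidable at little cost, so the change should be made.

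**What to change.** In the Statistical analysis section, and in the section on EEG data recording and treatment:

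1. Enter EEG band power, frequency and amplitude as continuous predictors, for example after log transformation.
2. Analyse the functional scales at full resolution: linear or rank-based regression for the MIF and DRS, proportional-odds regression for the FAC, RLA and GCS.
3. Keep binomial logistic regression for mortality.
4. Keep a good/poor split of a scale for the ROC and AUC analysis, with its cutpoint fixed in advance.

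If the binary analysis is to remain the main one for functional scores, replace the 80% under Description of protocol with the power of that analysis, stating the assumed split and number of EEG categories.

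The cost is a change of wording and effect measures that are slightly less simple to present. No extra patients, visits or software are needed, since Stata is already named and fits these models.

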## Limitations

The main limitation of this study is the lack of complementary materials with adequate methodological quality regarding the EEG biomarkers, which could provide more robust evidence to strengthen this protocol. In addition, the absence of consensus on which EEG biomarkers are most indicative of functional outcomes in patients with severe traumatic brain injury (TBI) remains a challenge for standardizing the analysis. The scarcity of previous studies in specific TBI populations, with varying etiologies and clinical characteristics, limits the generalization of findings to a broader context.

Another significant limitation is the difficulty in controlling all variables that may influence EEG activity, such as different treatments administered to patients, medication use, or even the presence of comorbidities. The variability in treatment protocols can influence EEG measurements, making the interpretation of results more complex and comparison with other studies more challenging.

Despite these limitations, the application of this protocol is both necessary and valid, as the clinical hypothesis, supported by indirect evidence, suggests that EEG biomarkers may be effective in predicting significant clinical outcomes in patients with severe TBI, with the potential to contribute to the development of new diagnostic and intervention strategies.

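### The stated model names only EEG predictors and plans no comparison with the clinical predictors already collected, so its AUC does not support the claimed improvement in prediction

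*Protocol article*

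**What the plan says.** All references are to the protocol article.

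- **Model (Statistical analysis).** The plan is to develop "a predictive model based on categorized characteristics, such as frequency bands and amplitudes of EEG signals, to correlate these parameters with clinical outcomes". The regression is described thus: "Binomial logistic regression analyses will be performed using Stata (version 17) to explore the predictive power of EEG biomarkers". For performance, "the area under the curve (AUC) will be calculated to evaluate the sensitivity and specificity of predictive models". Cross-validation and a Hosmer-Lemeshow test follow. No clinical covariate, reference model or test of an AUC gain is named.
- **Data available (Collection and clinical information).** Sociodemographic data are taken from the records, "including information on age, gender, education level, occupation, and other relevant factors". Hospital data include "vital signs, pupillary response characteristics, need for intubation, surgical interventions performed, imaging results". The section ties these to describing the patients and, loosely, to analysing variables related to TBI. It does not tie them to the EEG model.
- **Coma score (Table 1).** Entry requires "Glasgow Coma Scale (GCS) ≤ 8 at any time during hospital stay", so the qualifying score lies between 3 and 8.
- **Timing (Data collection protocol).** The EEG is recorded straight after transfer from the ICU to the ward. The functional scales are first taken at ICU discharge, so the two are nearly concurrent.
- **Sample size (Description of protocol).** 84 patients, for a two-tailed test of a Pearson correlation of 0.3 at α = 0.05 with power 0.80.
- **Claims.** The Abstract says that EEG monitoring combined with inflammatory markers makes outcome prediction better. The Protocol validation section says the same of prognostic assessment when abnormal patterns are identified early.
- **Limitations.** The article concedes "difficulty in controlling all variables that may influence EEG activity", naming treatments, medication and comorbidities.

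**The concern.** A claim that prediction improves needs something to improve on. The natural baseline is what the clinician already knows when the EEG is recorded: age, coma score, pupils and the functional score at ICU discharge. The Background says that EEG patterns go with injury severity, and Table 3 links increased delta activity to moderate-to-severe injury and coma. An EEG feature can therefore discriminate between good and poor outcome partly because it reflects severity that is already known. The AUC of a model containing only EEG features cannot separate that part from new information.

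At stake is the interpretation of a positive result. A significant association or a respectable AUC could be read as a reason to add EEG to prognostic assessment, although the stated analysis would not have tested whether EEG adds anything.

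**Working it through.** **Inputs.** From the article: N = 84, r = 0.3, two-sided α = 0.05, power 0.80. Assumed, because the article gives no figures: R, the correlation of a clinical score with outcome (0.4 to 0.6); c, the correlation of the EEG feature with that score (0 to 0.4); k = 4 clinical terms, one each for age, GCS, pupils and the ICU-discharge scale; an event share of 30% to 50%.

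**1. The plan's own figure.** Fisher z: n = ((1.960 + 0.842)/atanh(0.3))² + 3 = (2.802/0.3095)² + 3 = 84.9, rounded up to 85. Simulating the distribution of r under bivariate normality (1,000,000 draws) gives power 0.795 at n = 83 and 0.800 at n = 84. The stated 84 is reproduced, for one unadjusted correlation.

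**2. Can the planned effect arise with no added value?** If EEG relates to outcome only through severity, its marginal correlation is the product of the two links.
- 0.6 × 0.5 = 0.30. The partial correlation is zero, since 0.30 − 0.5 × 0.6 = 0, yet the marginal test is significant with power 0.80.
- 0.4 × 0.5 = 0.20. Power = Φ(atanh(0.20) × √81 − 1.960) = Φ(1.824 − 1.960) ≈ 0.45.

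This is a boundary case. It shows what a positive marginal result is compatible with, not what is likely.

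**3. Adjusted effect when the marginal correlation is 0.30.** Partial r = (0.30 − R·c)/√((1 − R²)(1 − c²)). Power = Φ(atanh(partial r) × √(84 − 4 − 3) − 1.960), with √77 = 8.775.

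Example, R = 0.5 and c = 0.3: (0.30 − 0.15)/√(0.75 × 0.91) = 0.15/0.826 = 0.182. Power = Φ(0.184 × 8.775 − 1.960) ≈ 0.36.

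| R | c | partial r | power at N = 84 |
|---|---|---|---|
| 0.4 | 0 | 0.327 | 85% |
| 0.4 | 0.2 | 0.245 | 59% |
| 0.5 | 0 | 0.346 | 89% |
| 0.5 | 0.3 | 0.182 | 36% |
| 0.6 | 0 | 0.375 | 93% |
| 0.6 | 0.4 | 0.082 | 11% |

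If EEG is unrelated to the clinical score, adjustment raises its correlation. If they overlap to the extent assumed here, adjustment lowers it. The EEG model by itself cannot tell these cases apart.

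**4. N for 80% power on the adjusted effect.** n = ((1.960 + 0.842)/atanh(partial r))² + 3 + 4.

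| partial r | power at N = 84 | N for 80% |
|---|---|---|
| 0.30 | 77.5% | 89 |
| 0.25 | 61% | 128 |
| 0.20 | 43% | 198 |
| 0.15 | 26% | 351 |

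**5. Events per term in the logistic model.** 0.30 × 84 = 25.2 and 0.50 × 84 = 42 events. Four clinical terms plus one EEG term leave 25.2/5 = 5.0 to 42/5 = 8.4 events per term. Four clinical terms plus the five bands of Table 3 leave 25.2/9 = 2.8 to 42/9 = 4.7. A reference model must therefore be small.

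Steps 2 to 4 use correlations. They carry over to binary outcomes and logistic regression only as an indication of scale.

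**The case against.** Four arguments can be made against the point.

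**The model is not said to exclude clinical variables.** A reader might infer that it uses EEG features alone. The text does not say so. The list of characteristics is open, the article speaks of predictive models in the plural, and some analytic use of the clinical data is foreseen. A covariate list is also often left to an analysis plan, which is not shown. This stands against the stronger reading. It does not remove the point: the article states the basis of the model, the performance measure, the validation, the fit test and the sample-size basis, all without a clinical comparator, and every example it gives is an EEG feature.

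**The study could still show added value.** This also stands. The needed variables are collected, so the gap lies in the stated analysis and not in the design.

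**Added value is not a stated aim.** The aim is the predictive potential of EEG, and the regression is described as exploratory. This is correct, and it is why the EEG model should stay and the increment need not become the main result. But the article does assert better prediction, and that assertion needs a comparison.

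**The overlap with severity is assumed.** All patients have severe injury and the qualifying GCS is confined to 3–8, which would weaken a correlation between EEG and GCS. The zero-added-value case requires that severity carry the whole EEG effect, and the article gives no evidence for that. This stands: the figures bound the question and do not answer it.

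Two further points are fair. The group comparisons in SPSS are labelled as initial and descriptive, so their lack of adjustment is no fault. The variance reduction that a baseline score brings in a linear model does not carry over to the planned logistic regression, so no such gain is claimed here.

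**Conclusion.** The point holds in a limited form. The Statistical analysis section names only EEG features as predictors and describes no comparison with the clinical predictors the study records. Followed as written, it yields EEG's marginal discrimination. That answers the narrow question of predictive potential but does not support the statements in the Abstract and the Protocol validation section that prediction or prognostic assessment is improved.

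It would go too far to say that the trial cannot show added value, that clinical variables are barred from the model, or that EEG merely re-measures severity. The documents support none of these.

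The size depends on correlations the article does not give. With a marginal correlation of 0.30 and R between 0.4 and 0.6, the adjusted correlation runs from 0.08 (c = 0.4, power about 11%) to 0.375 (c = 0, power about 93%). The sample size is not wrong for its stated purpose; it was not chosen for this comparison. The conclusion about the missing comparison does not rest on these figures.

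**What to change.** Keep the EEG model and add the following to the Statistical analysis section.

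1. A small prespecified clinical reference model: age, GCS and pupillary response. Where the outcome is a later functional score, add the ICU-discharge value of the same scale. That term does not apply to mortality. Penalise the terms or combine them into one linear predictor.
2. The same model with the EEG feature or features added. Report a likelihood-ratio test and the change in cross-validated AUC with its confidence interval.
3. A sentence limiting any claim of improved prediction to this comparison.
4. A statement that N = 84 was sized for one unadjusted correlation of 0.3, so the increment is reported as an estimate with its precision. A non-significant increment should not be read as evidence that EEG adds nothing.

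**Cost.** Analysis wording, no new data collection, and a few degrees of freedom. The reported EEG effect will probably be smaller, and power for the increment may be low. If the sponsor wants the increment as a confirmatory result, N needs its own justification; step 4 of the working shows 89 to 351 patients for adjusted correlations of 0.30 down to 0.15.
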